## Abstract

**Background:**

People of color (POC) who experience race-related stress are at risk of developing mental health problems, including high levels of stress, anxiety, and depression. Mindfulness meditation may be especially well suited to help POC cope, given its emphasis on gaining awareness and acceptance of emotions associated with discriminatory treatment. However, mindfulness meditation rarely reaches POC, and digital approaches could reduce this treatment gap by addressing traditional barriers to care.

**Objective:**

This study will test the effectiveness of a self-directed app-based mindfulness meditation program among POC who experience elevated levels of race-related stress. Implementation outcomes such as treatment acceptability, adherence, and satisfaction will be examined.

**Methods:**

Participants (n=80) will be recruited online by posting recruitment materials on social media and sending emails to relevant groups. In-person recruitment will consist of posting flyers in communities with significant POC representation. Eligible participants will be block randomized to either the intervention group (n=40) that will complete a self-directed 4-week mindfulness meditation program or a wait-list control condition (n=40) that will receive access to the app after study completion. All participants will complete measures at baseline, midtreatment, and posttreatment. Primary outcomes include changes in stress, anxiety, and depression, and secondary outcomes constitute changes in mindfulness, self-compassion, rumination, emotion suppression, and experiential avoidance. Exploratory analyses will examine whether changes in the secondary outcomes mediate changes in primary outcomes. Finally, treatment acceptability, adherence, and satisfaction will be examined descriptively.

**Results:**

Recruitment began in October 2021. Data will be analyzed using multilevel modeling, a statistical methodology that accounts for the dependence among repeated observations. Considering attrition issues in self-directed digital interventions and their potential effects on statistical significance and treatment effect sizes, we will examine data using both intention-to-treat and per-protocol analyses.

**Conclusions:**

To our knowledge, this will be the first study to provide data on the effectiveness of a self-directed app-based mindfulness meditation program for POC recruited based on elevated race-related stress, a high-risk population. Similarly, meaningful clinical targets for POC affected by stressors related to race will be examined. Findings will provide important information regarding whether this type of intervention is an acceptable treatment among these marginalized groups.

**Trial Registration:**

ClinicalTrials.gov NCT05027113; https://clinicaltrials.gov/ct2/show/NCT05027113

**International Registered Report Identifier (IRRID):**

DERR1-10.2196/35196

## Introduction

### Background

In the United States, people of color (POC) are disproportionally affected by stressors related to race and ethnicity compared with their non-Latinx White counterparts, with approximately 70% of POC reporting having experienced some form of discrimination in their lives and 60% reporting facing day-to-day discriminatory treatment [1,2]. The prevalence of these discriminatory experiences varies across POC groups, with Black individuals (70%) experiencing more instances of discrimination compared with their Asian (57%) and Latinx (45%) counterparts [1]. Notably, approximately 60% of Black, 49% of Asian, and 45% of Latinx individuals state that these experiences make their lives harder [2]. Race-related stress is the psychological distress associated with appraising a situation as disturbing or burdensome because of negative racial bias [3]. Race-related stressors have multiple forms, such as direct interpersonal discrimination (ie, perceived differential and unfair treatment among individuals), vicarious discrimination (ie, observing members of one’s race or ethnicity being victimized), and institutional practices (ie, laws and policies that limit access to services and opportunities) [4,5]. Common race-related stressors experienced by POC include being treated with less courtesy or respect, receiving poorer service, receiving unfair treatment in the workplace, and negative interactions with police [2].

### Race-Related Stress and the Mental Health of POC

When differential or unfair treatment is perceived as racially motivated, it triggers physiological (eg, cardiovascular reactivity, dysregulated hypothalamic-pituitary-adrenal axis activity), cognitive-affective (eg, rumination, emotion suppression), and behavioral (eg, avoidance, aggression) responses that prepare the individual to confront the situation [6-8]. The chronic and unpredictable nature of race-related stressors often depletes individuals’ psychological resources and increases their vulnerability to developing mental health disorders [8]. Meta-analytic work shows that based on effect sizes, stress (*r*=.27), anxiety (*r*=.22-.25), and depression (*r*=.21-.26) are the mental health problems most strongly correlated with experiencing race-related stress, and these associations seem to be stronger among Asian and Latinx individuals compared with Black individuals [9-11]. This disproportionate exposure to race-related stressors may partly explain the higher prevalence and persistence rates of mood and anxiety disorders among Black, Asian, and Latinx groups compared with non-Latinx White groups [12,13]. These adverse mental health outcomes are especially concerning considering current social events, including instances of police brutality [14], recent political discourse [15], the COVID-19 pandemic [16], and an increase in hate crimes [17] that have made race-related stressors even more salient, further affecting the mental health of POC communities.

Considering POC exposed to race-related stress are at high risk of developing a mental health disorder, there is a clear need for treatments that allow individuals to cope effectively with these stressors. Among numerous evidence-based treatments available, mindfulness meditation may be particularly well suited to help POC cope.

### Mindfulness Meditation for Race-Related Stress in POC

Mindfulness is a psychological trait associated with staying in the present moment with one’s experience (ie, physical sensations, thoughts, emotions, behaviors), endorsing a nonjudgmental and curious attitude, and cultivating acceptance and self-compassion [18]. Self-compassion refers to an attitude of openness to one’s own suffering without avoiding it, cultivating the desire to alleviate it without self-judgment [19]. Multiple meta-analyses have shown that increases in mindfulness and self-compassion are two of the mechanisms by which mindfulness meditation leads to decreases in overall stress, anxiety, and depression [20-24].

Furthermore, mindfulness meditation could be particularly effective in helping POC cope with race-related stress by reducing experiential avoidance. Experiential avoidance is the inability to remain in contact with distressing physical sensations, thoughts, and emotions, even when doing so causes harm in the long term [25]. POC exposed to race-related stressors often develop emotional (eg, unwillingness to experience sadness after being discriminated against) and behavioral (eg, evading places or situations where discrimination is anticipated to occur) avoidance that maintain mental health symptoms [5,6,8]. As such, mindfulness meditation, with its emphasis on bringing awareness to all experiences regardless of their negative valance, may serve as an exposure strategy that reduces avoidance, leading to decreases in psychological distress [26].

Considering that rumination (ie, the passive and repetitive focus on the causes and consequences of one’s distress) [27] and emotion suppression (ie, the active reduction of emotionally expressive behavior when emotionally aroused) [28] are maladaptive emotion regulation strategies often used by POC exposed to race-related stressors [5,6,8,29], researchers and clinicians have hypothesized that mindfulness meditation may be particularly well-suited for this population [30-32]. Research suggests that mindfulness meditation disrupts ruminative tendencies by cultivating acceptance of and nonjudgmental engagement with thoughts [33]. In the case of emotion suppression, mindfulness meditation may help individuals identify, describe, and healthily engage with emotions triggered by race-related stressors rather than suppress these feelings, leading to decreases in mental health symptoms [34].

Although research to date supports the effectiveness of mindfulness meditation in reducing mental health problems, most studies have relied on almost exclusively non-Latinx White samples [35], which significantly differ from POC on critical demographic variables, such as level of education, income, and culture (ie, norms, language, beliefs, customs). For example, even in a meta-analysis where the primary aim was to examine mindfulness meditation’s effectiveness among underserved populations, less than 30% of studies included had POC samples [30]. A more recent systematic review surveying literature from 1990 to 2016 found only 24 studies examining the effectiveness of mindfulness meditation in POC samples, and just 25% of these studies were conducted with adults [36].

### Improving Access to Mindfulness Meditation for POC via Technology

Despite the significant mental health need among individuals who experience race-related stress and the existence of promising interventions such as mindfulness meditation, POC face numerous barriers to care, including limited access to providers [37], financial and transportation constraints [38], and stigma [39]. Although no single approach will eliminate all barriers driving mental health disparities, using technology to provide care could reduce this treatment gap [40,41].

Among many technological resources available, smartphones represent a promising vehicle for providing mental health services. The feasibility of this approach is supported by extensive ownership of mobile devices in the United States. For instance, approximately 85% of Americans have a smartphone, with POC having similar ownership rates as non-Latinx White individuals [42]. Compared with non-Latinx White people, POC are also more likely to be smartphone-dependent, meaning they rely on these devices to access the internet in the absence of a broadband connection at home. As such, interventions using smartphones may be well positioned to reach those affected by the digital divide observed in low-income households, as these interventions capitalize on technology already owned by POC [40,43].

In addition to their feasibility, there is a growing body of evidence supporting the efficacy of app-based mental health interventions [44,45]. Although somewhat limited, existing data with POC samples are promising [40]. In the case of app-based mindfulness meditation, multiple meta-analyses show that these interventions effectively reduce overall stress, anxiety, and depression [46-48] and increase mindfulness and self-compassion [47,48]. To our knowledge, experiential avoidance, rumination, and emotion suppression have not been examined as potential clinical targets in app-based mindfulness meditation. Furthermore, similar to face-to-face mindfulness meditation research, there is a lack of POC representation in app-based mindfulness meditation studies.

### Issues of Engagement in App-Based Mental Health Interventions

Despite their feasibility and empirical support, there are significant concerns regarding treatment engagement in app-based mental health interventions. Enrollment rates are low, with a meta-analysis showing that 8% to 58% of participants never download the intervention app [49]. Even when the app is downloaded, studies show that some users never use it, and those who engage with the app are unlikely to do so more than a few times, showing a decrease in use over time [49,50]. Similarly, attrition rates range from 24% to 53%, with higher rates found in longer programs (ie, more than 8 weeks) [49]. Importantly, programs without guidance (eg, via human coach, automated reminders) seem to lead to even poorer treatment engagement [51]. This limited treatment engagement in app-based mental health interventions is concerning as users may not receive enough treatment dosage to promote behavioral change.

Considering the importance of promoting treatment engagement for the success of app-based interventions, researchers and clinicians have proposed multiple strategies to increase acceptability, improve adherence, and reduce attrition. Among numerous approaches to promote app user engagement, cultivating a sense of guidance and support may be especially effective. Onboarding procedures in which users interact with providers before starting the intervention, asking questions about the intervention, problem-solving potential barriers to engagement, and building a relationship with the team have shown to be associated with higher treatment engagement [52]. Similar procedures in app-based interventions for POC seem to be effective as users can ask questions about the program and request assistance with technology [53]. As a whole, studies show that onboarding procedures decrease treatment attrition in app-based mental health interventions [49].

Among POC who have more limited access to technology, the use of text messaging notifications could be a especially well-suited strategy to increase treatment engagement. Text messages capitalize on the high phone ownership rates among POC while minimizing costs, as most phone plans include unlimited text messages. The feasibility of this approach is supported by previous studies showing that receiving simple text messaging reminders increases attendance to face-to-face treatment sessions among POC [54,55]. Importantly, this engagement strategy is well tolerated by participants [56]. These findings among POC are consistent with other studies showing that receiving prompts (eg, text messages, app notifications) leads to higher treatment engagement in digital interventions [57]. In app-based interventions, the use of prompts has also been found to be associated with lower attrition rates [49]. Therefore, exploring treatment acceptability, adherence, and satisfaction in these programs is crucial to determining whether mindfulness meditation programs are relevant for POC who experience race-related stress.

### This Study

Considering the lack of research examining the effectiveness of mindfulness meditation among POC, especially those who experience elevated levels of race-related stress, this study will use a randomized controlled trial (RCT) approach to examine whether receiving an app-based mindfulness meditation intervention leads to decreases in the adverse mental health outcomes more often associated with exposure to race-related stress (ie, stress, anxiety, depression) among POC. Similarly, this RCT will test whether the intervention engages hypothesized mechanisms of change (ie, mindfulness, self-compassion, experiential avoidance, rumination, emotion suppression). As an exploratory aim, this study will examine whether decreases in the primary outcomes of interest (ie, stress, anxiety, depression) occur via hypothesized mechanisms of change (ie, mindfulness, self-compassion, experiential avoidance, rumination, emotion suppression). Finally, acceptability, adherence, and satisfaction will be analyzed descriptively. Results from this trial will contribute to the nascent data on mindfulness meditation’s acceptability and effectiveness with POC. To our knowledge, this study will be the first to include a sample of POC recruited based on elevated levels of race-related stress, a high-risk population that is not commonly targeted in mindfulness meditation research.

## Methods

### Participants

A power analysis using G*Power [58] indicated that, based on 2 groups (ie, control vs active treatment), 3 repeated measurements (ie, baseline, midtreatment, posttreatment), a conservative *r*=.60 correlation among repeated measures, and a small *d*=0.2 treatment effect size, a sample of n=54 provides 95% power to detect a treatment by time interaction using the most conservative outcome in this study. Considering recent meta-analytic work suggesting an approximately 24% attrition rate in short-term (ie, 4 weeks or less) mindfulness meditation app trials with at-risk samples [49], we plan to recruit 80 POC individuals for this study.

Individuals interested in participating in this study will complete an online screening questionnaire using Qualtrics, a platform that is smartphone compatible. For study inclusion, participants are required to (1) self-identify as a member of a POC group (eg, Black/African American, Asian/Asian American/Pacific Islander, Latinx, Native American/Native Alaskan, multiracial, other), (2) report experiencing elevated levels of race-related stress (ie, a score of 55 or higher on the Index of Race-Related Stress–Brief [IRRS-B] [4] or a score of 12 or higher on the Multicultural Discrimination Module [MDM] [59]), (3) speak and read English, (4) not receive psychological services currently (ie, individual or group therapy, any type of counseling), (5) not have practiced mindfulness meditation for more than 2 hours in the month prior to study commencement, (6) own a smartphone with access to the internet, (7) be willing to install the mindfulness meditation app and accept daily notifications and text reminders, and (8) be aged 18 years or older.

Those individuals who meet eligibility criteria will be contacted by a research team member to obtain verbal consent and randomize them to either the intervention group (n=40) or a wait-list control group (n=40) using block randomization. During this onboarding procedure, participants in the intervention group will be assisted in installing the mindfulness meditation app, setting app notifications, understanding daily text messaging reminders, and getting familiar with the intervention content. Similar onboarding procedures have been shown to improve treatment adherence in app-based mindfulness meditation studies [49,51]. Participants in the control condition will be reminded of the scheduled assessments and when they will receive access to the mindfulness meditation app (ie, 4 weeks after randomization). Individuals who endorse self-harm or suicidal ideation during the onboarding procedure or in their replies to the text messages will be further assessed and referred to crisis support services.

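### n=54 gives 95% power for Cohen's f=0.20, not for the stated d=0.2, where power is about 41% at alpha .05

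*Protocol article*

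**What the plan says.** The only justification of sample size is in the protocol article, Methods, Participants. It names G*Power and lists the inputs: two groups, "3 repeated measurements (ie, baseline, midtreatment, posttreatment") and "a conservative *r*=.60 correlation among repeated measures". From these it concludes that, for "a small *d*=0.2 treatment effect size, a sample of n=54 provides 95% power to detect a treatment by time interaction". It then cites about 24% attrition and says "we plan to recruit 80 POC individuals for this study". Alpha, the effect-size option and the sphericity setting are not given, and Cohen's f is not mentioned.

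The Results section names the group-by-time interaction as the contrast of primary interest, so this sentence is meant to power the main comparison.

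**The concern.** G*Power's repeated-measures interaction procedure takes the effect size f, not d. A d of 0.2 is small. To detect it with 95% power from 54 people and a within-person correlation of .60 would be surprising. The likely explanation is that 0.2 went in as f and was reported as d.

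The label matters because it sets what the trial is believed able to show. As written, the trial appears almost certain to detect a small benefit on stress, anxiety or depression. A reader meeting a null result could then conclude that even a small effect had been ruled out in this understudied population, when the design would miss such an effect more often than not.

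**Working it through.** **Inputs.** From Methods, Participants: k=2 groups, m=3 measurements, ρ=.60, N=54, effect 0.2, power 95%, attrition 24%, planned recruitment 80. Assumed, because not stated: alpha .05 and sphericity (the favourable setting).

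**Formula** (G*Power's default for the within-between interaction): λ = f²·N·m/(1−ρ), df1 = (k−1)(m−1) = 2, df2 = (N−k)(m−1) = 2(N−2). Power is the upper tail of the noncentral F beyond the central critical value.

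**1. Reproducing the stated figure, with 0.2 as f.**
- N=53: λ = 0.04×53×3/0.4 = 15.9, power 94.99%.
- N=54: λ = 0.04×54×3/0.4 = 16.2, df 2 and 104, power 95.36%.

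So 54 is exactly the smallest N that reaches 95%.

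**2. The stated effect, d=0.2.** For two groups f = d/2 = 0.10.

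| N | λ | Power |
|---|---|---|
| 54 | 0.01×54×3/0.4 = 4.05 | 41% |
| 61 (80×0.76 = 60.8) | 4.575 | 46% |
| 80 | 6.0 | 58% |
| 130 | 9.75 | 80% |
| 208 | 15.6 | 95% |

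**3. What f=0.20 means as a treatment effect.** Let the arms be equal at baseline and differ by δ (in SDs of the outcome at one visit) at week 4. The interaction f² is the mean over visits of ((visit difference − average difference)/2)².
- Linear growth (0, δ/2, δ): f² = δ²/24, so f=0.20 is δ = 0.20×√24 = 0.98.
- Step (0, δ, δ): f² = δ²/18, so f=0.20 is δ = 0.20×√18 = 0.85.

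Conversely, if d=0.2 means δ=0.2, then f = 0.041 (linear) or 0.047 (step). Power is 10% or 12% at N=54, and 13% or 16% at N=80.

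**4. Detectable effect at 80% power.**
- N=61: f=0.147, so δ is 0.147×√18 = 0.62 (step) to 0.147×√24 = 0.72 (linear).
- N=80: f=0.128, so δ is 0.54 (step) to 0.63 (linear).

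**5. Other readings of d=0.2 at N=54.**

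| Reading | Power |
|---|---|
| Interaction, f=0.10, alpha .10 | 54% |
| Interaction, f=0.10, nonsphericity ε=0.75 | 35% |
| Interaction, f=0.10, G*Power's SPSS-style or Cohen-1988 effect-size option | 13% to 14% |
| Between-group test, f=0.10 | 13% |
| t test on week-4 score | 11% |
| t test on change from baseline | 13% |
| ANCOVA at week 4 | 15% |
| ANCOVA on the mean of both follow-ups | 19% (29% one-sided) |

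None comes near 95%. With f=0.10, N=54 reaches the same λ of 16.2 only if ρ=.90, since 0.01×54×3/0.10 = 16.2; the article fixes ρ at .60.

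**6. The attrition step is sound.** 54/0.76 = 71.05, so 72 would be needed, and 80 exceeds that.

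**The case against.** The core arithmetic cannot be faulted, but several qualifications are fair.

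- **Alpha is unstated**, so 41% is conditional on .05 and sphericity. This stands. Alpha .10 raises the figure to 54%, still far short of 95%.
- **The G*Power settings are not shown**, so that 0.2 was entered as f is an inference. This stands, though the exact match at N=54 makes it very likely. The error does not depend on it: the stated d does not give the stated power.
- **Intention-to-treat uses everyone randomised.** Results defines that analysis on all allocated participants with the last observation carried forward, so its sample is 80, not 61. This stands, and 58% belongs beside 46%. Carried-forward values may dilute the effect, so 58% is better read as an upper figure.
- **To say that only large effects are detectable would go too far.** This stands at 80% power, where the detectable difference is 0.54 to 0.72 SD across the two sample sizes. The 0.85 to 0.98 SD range belongs to f=0.20, that is, 95% power at n=54.
- **The article never claims that a null result would exclude a small effect**, and it admits that the sample is relatively small. True, but a claim of 95% power for d=0.2 invites that reading.
- **Nothing in the conduct changes.** Also true. That makes the correction cheap; it does not make the published figure right.

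**Conclusion.** The power statement is wrong as written and must be corrected. At n=54, 95% power holds for f=0.20 (d=0.4 by the usual two-group conversion), not for d=0.2. For d=0.2 taken as f=0.10, power is 41% at n=54, 46% with about 61 completers and 58% with all 80. For a 0.2 SD difference in change at week 4 it is 10% to 16% across n=54 to n=80.

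These figures rest on the article's own inputs plus alpha .05 and sphericity; the SD-of-change figures also assume equal baselines and either linear growth or a step. The size of the gap to 95% means that no plausible choice among these assumptions rescues the claim.

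**What to change.** In Methods, Participants, rewrite the power sentence so that it:

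1. gives the effect size as f=0.20 and states alpha, the effect-size option and the sphericity assumption;
2. translates that effect into one clearly defined quantity, preferably the difference between arms in change from baseline to week 4: about 0.85 SD (step) to 0.98 SD (linear);
3. drops the description of the effect as small;
4. reports what the planned sample delivers on that same scale: at 80% power, a detectable difference of about 0.62 to 0.72 SD with 61 completers and 0.54 to 0.63 SD with all 80; for a 0.2 SD difference, power of 13% (linear) to 16% (step) even with all 80. If d=0.2 is kept by the f=d/2 conversion, say so and give 46% (n=61) and 58% (n=80).

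The trial report should not read a non-significant interaction as evidence against a small effect; confidence intervals should carry that interpretation.

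The cost is a few sentences and a less favourable published figure. Enrolment, randomisation, outcomes and analysis model need not change on this account.
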